### Safety evaluation

3.3

All adverse events will be recorded on paper CRFs by the acupuncturist, including the time of occurrence, severity, management, and their relationship to the intervention. Mild adverse events will include minor bleeding, bruising, acupuncture-related pain, and localized infection; serious events will include organ injury and uncontrolled hemorrhage. In the event of serious adverse events, the intervention will be stopped immediately, appropriate treatment will be provided, and the event will be reported to the Institutional Review Board within 24 h.

The timeline for each assessment is detailed in Table 2.

**Table 2 tab2:** Timeline of each assessment.

Outcomes	Intervention			Follow-up	
	Week 0	Week 1	Week 2	Week 4	Week 6
Weekly spontaneous bowel movements		**×**	**×**	**×**	**×**
Bowel movement regularity		**×**	**×**	**×**	**×**
Rescue medication use		**×**	**×**	**×**	**×**
Bowel sounds	**×**	**×**	**×**		
Abdominal circumference	**×**	**×**	**×**		
Glasgow coma scale	**×**	**×**	**×**	**×**	**×**
National institutes of health stroke scale	**×**	**×**	**×**	**×**	**×**
Modified rankin scale	**×**	**×**	**×**	**×**	**×**
Length of hospitalization					×
Safety evaluation					

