### Randomization and blinding

2.3

Eligible participants will be randomly and equally assigned to the EA group or the sham electroacupuncture (SEA) group using a central web-based randomization system (http://47.119.117.255). The randomization sequence will be generated with a block size of 4. An independent researcher, who is not involved in outcome assessment, will perform the randomization and group allocation.

Since acupuncture involves manual procedures, only the acupuncturists will be unblinded. Outcome assessors, physicians, nurses, caregivers, patients, and statisticians will all remain blinded. An independent monitor will be responsible for maintaining the integrity of the blinding process.

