### Data management

2.5

Study data will be recorded on case report forms (CRFs) by assessors, with participants identified by randomization numbers. Two independent staff will perform double data entry. The data management system will validate entries for range and logic errors. All data will be encrypted, with access restricted to authorized personnel. Paper CRFs will be securely stored at the South China Research Center for Acupuncture and Moxibustion for no less than three years after the completion of the study.

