### Statistical analysis

2.8

This study will employ both intention-to-treat analysis and per-protocol analysis. The intention-to-treat analysis will include all randomized participants, while the per-protocol analysis will focus on those with good compliance and no major protocol violations. The safety analysis set will comprise participants who receive at least one intervention and have safety evaluations.

All statistical analyses will be conducted using SAS software (version 9.4; SAS Institute Inc., Cary, NC, USA). Two-sided tests will be used, with *p* < 0.05 considered statistically significant. Continuous variables will be assessed for distribution using histograms and Q–Q plots, and reported as mean ± standard deviation (SD) or median (interquartile range, IQR), as appropriate. Categorical variables will be presented as counts (n) and percentages (%). Between-group comparisons will use independent t-tests or Mann–Whitney U tests for continuous variables, and Chi-square or Fisher’s exact tests for categorical variables.

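### The only unblinded staff record every adverse event and judge its severity and causality, which leaves the between-arm safety comparison open to bias of unknown direction and size

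*Protocol article*

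**What the plan says.** **Who records.** Section 3.3 (Safety evaluation): "All adverse events will be recorded on paper CRFs by the acupuncturist", "including the time of occurrence, severity, management, and their relationship to the intervention".

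**Who is blinded.** Section 2.3 (Randomization and blinding): "only the acupuncturists will be unblinded". The same section adds: "Outcome assessors, physicians, nurses, caregivers, patients, and statisticians will all remain blinded".

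**Who completes the forms in general.** Section 2.5 (Data management): "Study data will be recorded on case report forms (CRFs) by assessors".

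**Examples of events.** Section 3.3: "Mild adverse events will include minor bleeding, bruising, acupuncture-related pain, and localized infection"; "serious events will include organ injury and uncontrolled hemorrhage".

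**Analysis.** Section 2.8 (Statistical analysis) compares adverse events between groups by chi-square or Fisher's exact test. The safety set is limited to "participants who receive at least one intervention and have safety evaluations".

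**The concern.** Whether an event is noticed, how severe it is and whether the intervention caused it are partly matters of judgement. Here they are assigned to the person who delivered the treatment and knows whether it was real or sham. The two procedures cannot be mistaken by that person: one uses penetrating needles with current (section 2.4.1), the other blunt needles without current (section 2.4.2). Any difference in attention or attribution between arms passes straight into the test in section 2.8. Section 3.3 describes no blinded adjudication.

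Safety is part of the stated aim at the end of the Introduction, and the Discussion looks forward to calling the treatment safe in critically ill stroke patients. Attribution made with knowledge of the allocation cannot be made blind after data collection. The staffing is also unclear, because sections 2.5 and 3.3 name different recorders.

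**Working it through.** The plan gives no figure on this point, so the check is mainly a comparison of sections.

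1. *Recorder.* Section 3.3 names the acupuncturist for all adverse events, not only for those at the needle site. The article therefore fixes this choice itself and does not leave it to a fuller document.
2. *Blinding.* Section 2.3 lists every other clinical role as blinded. Assessors and physicians who could collect and judge events blind are already in the trial.
3. *Conflict.* Section 2.5 gives form completion to assessors, and section 3.3 gives it to acupuncturists for adverse events. Section 3.3 may be meant as an exception, but neither section says so. I assume that the assessors of section 2.5 are the blinded outcome assessors of section 2.3.
4. *Use of the data.* Section 2.8 tests the recorded events between arms, so recording differences and true differences cannot be separated.
5. *Safety set.* Membership needs both an intervention and a safety evaluation. A treated patient who has no safety evaluation can be dropped.
6. *Deaths.* Section 3.2 scores death as mRS 6, and Table 2 schedules mRS to Week 6. Deaths are thus captured by an outcome scale, but section 3.3 does not say how they relate to its serious events.

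**Illustration on assumed values.** The article's sample size gives the arm size: 40 / (1 − 0.20) = 50 per arm, 100 in total, as section 2.7 states. Let the true event risk p be the same in both arms, and let a share c of events be recorded.

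Recorded risk = p × c, and the apparent risk ratio = (p × c₁) / (p × c₂) = c₁ / c₂, whatever p is.

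| Assumed recording, EA vs sham | Apparent risk ratio | Expected recorded events at p = 0.20 | at p = 0.40 | at p = 0.60 |
|---|---|---|---|---|
| 90% vs 90% | 1.00 | 9 vs 9 | 18 vs 18 | 27 vs 27 |
| 70% vs 90% | 0.78 | 7 vs 9 | 14 vs 18 | 21 vs 27 |
| 50% vs 90% | 0.56 | 5 vs 9 | 10 vs 18 | 15 vs 27 |

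By the normal approximation, a two-sided 0.05 test would falsely favour EA in about 8%, 13% and 22% of trials in the second row (p = 0.20, 0.40, 0.60), and in about 21%, 43% and 69% in the third. The nominal rate in that direction is 2.5%. Exchanging the two recording rates gives the same percentages against EA.

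**The case against.** The case for the present arrangement is not empty. The sham needle does not penetrate the skin, so bleeding, bruising or puncture marks can reveal the allocation. Keeping such events away from blinded assessors protects the efficacy outcomes. This stands for local events, and the fix keeps it. It does not explain why systemic or neurological events, and causality for all events, should go to the acupuncturist.

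It is also fair that bowel movements per week are the only confirmatory endpoint and are unaffected, and that the article mentions general monitoring (the Abstract, section 2.6). That monitoring does not change who records or attributes events.

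A reader might infer more than the article supports:

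- *Recording stops at Week 2.* Treatment ends then, but section 2.4.5 does not say who conducts the Week 4 and 6 follow-up, and the Abstract promises adverse event recording for the whole study. The empty safety row in Table 2 may come from text extraction and carries no weight here.
- *Only needling injuries count as serious.* The lists in section 3.3 are introduced as inclusive examples and are not closed. Fuller criteria may stand in a document not shown.
- *Early deaths are removed.* The safety-set wording can drop a treated patient without an evaluation. It does not say that a recorded death is no evaluation, and deaths also appear as mRS 6.
- *The bias favours EA.* Under-recording in the EA arm is possible. So is over-recording, because real needling leaves visible marks and invites attribution.

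**Conclusion.** The point holds as a risk of bias built into a stated choice. It is not a demonstrated bias. The sections cited show that the one unblinded role records and attributes all adverse events, that this disagrees with section 2.5, and that the result is tested between arms. Direction and size are unknown. The risk ratios of 0.78 and 0.56 rest wholly on assumed recording rates and vanish when recording is equal.

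The change should be made, because unblinded attribution cannot be repaired later and blinded staff are already available. It is not critical to the trial's main conclusion: the primary analysis and the sample size do not depend on it.

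**What to change.** - Have the blinded assessors collect adverse events at the existing Week 1, 2, 4 and 6 contacts, and have blinded physicians judge severity and causality.
- Let acupuncturists record only local procedure-site events, on a separate form and in a separate table, so that needle marks do not unblind the assessors. State that these events were recorded unblinded.
- Reconcile sections 2.5 and 3.3 on who completes the adverse event pages.
- Report deaths by arm, using the mRS 6 data already planned.
- Define the safety set as all participants who received at least one session, and report how many of them have no safety evaluation.
- Ask the sponsor to reconcile the serious-event examples in section 3.3 with the death outcome in section 3.2. Because seriousness also triggers stopping of the intervention, its definition is for the sponsor, and no rule is proposed here.

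The cost is a form and wording change and a few more minutes per visit. One limit remains: local events stay unblinded, and a visible mark may still reveal the allocation to an assessor who examines the abdomen.

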## Discussion

4

This study represents the first RCT specifically designed to evaluate the efficacy of EA in treating severe stroke-related paralytic ileus. While EA has been explored in postoperative ileus (18, 19), its application in critically ill stroke patients remains under-investigated.

The therapeutic effects of EA on paralytic ileus are hypothesized to involve multiple potential pathways. First, EA may modulate autonomic nervous function, particularly by enhancing vagal tone (30). Second, EA could regulate gastrointestinal hormones, such as motilin and gastrin, thereby improving intestinal peristalsis (31). Third, EA may exert anti-inflammatory effects by reducing pro-inflammatory cytokines, thus alleviating gut dysmotility (32). Additionally, emerging evidence suggests EA may alter gut microbiota composition (33), potentially restoring a favorable intestinal microenvironment conducive to motility recovery.

Compared with previous studies (18, 19) that predominantly focused on postoperative ileus and relied heavily on single-endpoint measurements such as time to first flatus or defecation, the present trial provides two significant methodological advancements. First, we selected WSBM as the primary outcome, which offers a continuous and objective measurement of sustained bowel function recovery, especially advantageous in stroke patients who cannot accurately report symptoms (7, 34). Unlike time to first flatus or defecation, it captures sustained improvements, offering a more meaningful efficacy assessment. Second, we employed a rigorous sham-controlled design using placebo needles, enhancing blinding effectiveness and reducing biases arising from patient expectations, thereby improving the internal validity and reliability of the findings (23).

Clinically, the findings from this trial could substantially influence practice by validating EA as an effective and safe therapeutic option for managing gastrointestinal dysfunction in critically ill stroke patients. If effective, EA may become an integral part of multimodal treatment strategies in intensive care units, thereby enhancing patient recovery, reducing the use of pharmacological laxatives, and improving overall quality of care. Moreover, positive results could support the wider clinical adoption of acupuncture-based interventions, potentially reducing complications related to impaired gut motility, shortening hospitalization, and informing future guideline recommendations for the management of stroke-related paralytic ileus.

This multicenter trial may face challenges in ensuring the consistency of acupuncture procedures across different study sites. First, all acupuncturists will undergo standardized training and obtain certification prior to patient enrollment, with continuous quality control measures implemented throughout the study to ensure procedural fidelity. Although no formal blinding index will be conducted, the use of a validated patient-blinded auxiliary device, together with centralized monitoring, is expected to maintain the integrity of blinding and minimize inter-centre variability. Second, potential adherence issues, particularly in the critical care context, will be addressed through enhanced communication strategies, structured education for healthcare providers, and routine follow-up with patients and their families. Third, for patients with impaired consciousness, a multidimensional outcome assessment system will be adopted to ensure objectivity and reliability in evaluations. Finally, all intercurrent events and instances of missing data will be systematically recorded. Sensitivity and subgroup analyses will be conducted to assess their potential impact on the study outcomes and to ensure the robustness of the results.

In conclusion, this rigorously designed RCT is expected to provide robust evidence for the efficacy and safety of EA in severe stroke-related paralytic ileus, while also offering important translational insights that may inform clinical decision-making and future guideline development.
